#### 2.6.1. Aim 1: Treatment effectiveness

##### 2.6.1.1. Outcome measures CAPS-5, ITQ, and DES

To investigate the effectiveness of the three treatment conditions, the average scores will be estimated for the outcome variables at each time point for the three conditions. The baseline values will be included as covariate in the model. This will result in 3 (Condition: EMDR, EMDR 2.0, and Flash) × 2 (Time: T8 and T12) average score estimates. To investigate the differential effectiveness in reducing PTSD, complex PTSD and symptoms of dissociation of the treatments, these average score estimates will be compared across the three conditions. To answer the research question if the treatment arms are effective in reducing PTSD, complex PTSD, and symptoms of dissociation over time, the average scores of measurement occasions T0 vs. T8 and T0 vs. T12 will be compared using *t*-tests.

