### 2.5. Sample size

To perform a power analysis for a multilevel model, it is required to estimate parameters based on earlier research (83), which was not possible for the interventions investigated in the current study. Power analyses were performed in G*Power 3.1.9.2, based on three pairwise comparisons between the conditions (EMDR therapy vs. EMDR 2.0, EMDR therapy vs. Flash, EMDR 2.0 vs. Flash) on the post-treatment measurement occasion. The power analysis is based on a two-sided *t*-test, in which two independent means will be compared with a Bonferroni-corrected alpha for the three pairwise comparisons = 0.0167 (0.05/3), power = 0.80 and Allocation ratio = 1. We aim to be able to detect a clinical meaningful difference between the conditions, what comes down to a medium to large effect size *d* = 0.65. To increase the power, we will include the baseline CAPS-5 score as a covariate in the analyses (84). By doing so, we expect to explain approximately a quarter of the variance at the post-treatment measurement. The residual variance reduces and gives us a sample size of *n* = 39 per condition, or *N* = 117 in total. To account for an expected 10% dropout, we will recruit a total 130 participants.

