### 2.6. Data analyses

The statistical analyses will be performed on an intention-to-treat basis. Pre-treatment group differences are assessed using one-way ANOVAs for continuous data and χ2 tests for categorical data. A multilevel model will be performed with Treatment Condition (EMDR therapy vs. EMDR 2.0 vs. Flash technique) and Time (weekly assessments during the treatment and bi-weekly assessments during the follow-up phase) as predictors in the model. Measurements are nested within participants. Multilevel models are preferred over a repeated-measures ANOVA as participants with missing data can be included. In Level 1 of the model, the outcome measures vary within participants over time. In Level 2 of the model, the intercepts and slopes of the growth trajectories vary between participants. All analyses will be performed using the statistical programs R (Version 4.2.2) and IBM SPSS (Version 28).

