There are some limitations of the study design that need to be addressed. First, a limitation includes the risk of missing data, due to numerous measurement occasions after the treatment phase. However, by using a statistical method that handles missing data well, we mitigate the impact of missing data on the statistical power. Furthermore, a limitation of the present study is that the participants are not blinded to their treatment conditions. This makes the design susceptible to expectancy effects of the participants. However, we do not anticipate that these expectancy effects will be stronger for one condition than for another, and the randomization process should account for an even distribution if these effects would occur. Another limitation is the absence of an inactive control condition. To this end, on the one hand, our study is a suboptimal design for testing the hypotheses that the experimental conditions are effective treatments for PTSD. In contrast, the active control condition in this study has been frequently compared to wait-list control conditions (7, 8), showing that EMDR therapy was more effective in the treatment of PTSD than wait-list control conditions. Therefore, we can assume that when EMDR 2.0 and the Flash technique have comparable effect sizes in comparison with EMDR therapy, these interventions are likely to be more effective than a waitlist control condition in the treatment of PTSD. Finally, a limitation of the present study is that the design and sample size will not yield enough statistical power to detect small effect sizes when comparing the treatment conditions or when investigating moderators of effectiveness.

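### The within-arm effectiveness t-tests on CAPS-5, ITQ and DES do not come from the stated model and are uncontrolled, and the fallback to comparable effect sizes has no criterion

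*Protocol article*

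**What the plan says.** All passages are in the protocol article.

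- **Section 2.6.1.1 (CAPS-5, ITQ, DES).** Baseline enters the model as a covariate, and the model yields three conditions by two occasions (T8 and T12) of mean estimates. To decide whether the arms are effective over time, "the average scores of measurement occasions T0 vs. T8 and T0 vs. T12 will be compared using" *t*-tests. The type of *t*-test and the handling of missing values are not stated.
- **Section 2.6.** The analyses are intention-to-treat, and "Multilevel models are preferred over a repeated-measures ANOVA as participants with missing data can be included".
- **Section 2.6.1.2.** For PCL-5, BDI-II, BSI and AAQ-II, effectiveness is judged by the effect of time in a multilevel model.
- **Section 2.5.** "The power analysis is based on a two-sided" *t*-test, with "Bonferroni-corrected alpha for the three pairwise comparisons = 0.0167 (0.05/3), power = 0.80 and Allocation ratio = 1". The target is a difference: "We aim to be able to detect a clinical meaningful difference between the conditions", set at *d* = 0.65. Through the baseline covariate, "we expect to explain approximately a quarter of the variance at the post-treatment measurement". For losses: "To account for an expected 10% dropout, we will recruit a total 130 participants".
- **Section 3 (Discussion).** The lack of an inactive control is named as a limitation. The text then argues that "we can assume that when EMDR 2.0 and the Flash technique have comparable effect sizes in comparison with EMDR therapy", the new treatments are likely to be better than wait-list.

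**The concern.** Whether EMDR 2.0 and the Flash technique work is part of Aim 1 (section 1.4) and the first clinical implication drawn in the Discussion. Two routes lead to that conclusion, and each has a gap.

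The first route is change within each arm. On CAPS-5, ITQ and DES the contrast needs a T0 mean that the stated model does not produce. An ordinary paired *t*-test would fill the gap by using only participants who have both values, although section 2.6 chose multilevel models to avoid such losses. Whatever the mechanics, the change has no untreated comparison. All participants enter with PTSD and are seeking treatment, so a fall also contains regression to the mean and natural recovery.

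The second route is the argument from comparable effect sizes. It is the only one that uses a randomised comparison, and it has no margin, interval rule or other criterion. The sample size was set to detect a difference, not to exclude one.

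**Working it through.** **1. The plan's own sample size.** Inputs from section 2.5: two-sided alpha 0.05/3 = 0.0167, power 0.80, *d* = 0.65, 25% of variance explained. Residual SD = √0.75 = 0.866, so the effective *d* = 0.65/0.866 = 0.751. A two-sample *t*-test then needs 39 per arm (power 0.804), 117 in total, and 117/0.90 = 130. The stated 39, 117 and 130 are reproduced, so the sample size is not at fault.

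**2. Model output against the test.** The model in section 2.6.1.1 has T0 on the right-hand side and gives means at T8 and T12. The test needs T0 against T8 and T0 against T12. T0 is not among the six estimates listed, so the contrast must come from outside that list.

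**3. Size of the missing-data problem if only complete pairs are used.** Overstatement of mean change = proportion lost × (change in completers − change in dropouts). Assume completers change by 1.0 SD and dropouts by 0 to 0.5 SD; the documents give neither figure.

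| Loss | Remaining of 130 | Overstatement |
|---|---|---|
| 10% (section 2.5) | 117 | 0.10 × (1.0 − 0.5) = 0.05 to 0.10 × (1.0 − 0) = 0.10 SD |
| 18% (EMDR treatment dropout cited in section 1.1) | about 107 | 0.18 × 0.5 = 0.09 to 0.18 × 1.0 = 0.18 SD |

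**4. What the paired test responds to.** With 39 pairs and two-sided alpha 0.05, power is 80% at a change of 0.46 SD of the differences. Assume equal SDs at both occasions and a correlation of √0.25 = 0.5. The SD of the differences is then √(2 × (1 − 0.5)) = 1.0 SD. A change of 0.3, 0.4 or 0.5 SD from any cause is significant 45%, 68% or 86% of the time. The test cannot tell treatment from natural course.

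**5. What a between-arm comparison can exclude.** SE = √(2/39 × 0.75) = 0.196 SD.

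- 95% half-width, *t* on 75 df: 1.99 × 0.196 = 0.39 SD.
- 98.3% half-width (the Bonferroni level): 2.45 × 0.196 = 0.48 SD.
- Chance of a non-significant result at alpha 0.0167, normal approximation (critical value 2.394), Φ(2.394 − δ/0.196): 81% for a true difference δ of 0.3 SD, 64% for 0.4 SD, 44% for 0.5 SD.

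**6. Power to show non-inferiority at 39 per arm.** This assumes no true difference and a one-sided 0.025 limit; power = Φ(margin/0.196 − 1.96). The margins are illustrative, since the documents state none.

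| Margin (SD) | Power |
|---|---|
| 0.30 | 33% |
| 0.325 (half of 0.65) | 38% |
| 0.40 | 53% |
| 0.50 | 72% |
| 0.65 | 91% |

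The smallest margin with 80% power is (1.96 + 0.84) × 0.196 = 0.55 SD.

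**The case against.** The strongest reply has four parts.

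- **Missing data.** A reader might infer that the plan leaves participants with missing data out of the *t*-tests. No sentence says so. Section 2.6 declares intention-to-treat, and the T0 mean could be subtracted from a model-based mean at T8 evaluated at the average baseline. That stands: exclusion is the natural reading of a T0-versus-T8 *t*-test, not a stated rule. What remains is that the article pairs a model without a T0 estimate with a test that needs one.
- **Reliance on *t*-tests.** PCL-5, also a primary measure, is tested by a multilevel time effect, which can keep participants with missing values. That stands for missing data. It does not help with attribution, because the time effect is equally uncontrolled.
- **Disclosure.** The Discussion calls the design suboptimal for this hypothesis and concedes low power for small effects, and section 1.4 says effectiveness is judged by change over time. This lowers the weight of the point. The conclusion drawn in the Discussion still goes further than change over time allows.
- **Comparability.** A reader might infer that any non-significant difference will be called comparable, or that almost any fall will be called effective. The documents support neither. The Discussion speaks of effect sizes, hedged, and sets no decision rule; a 0.3 SD change would reach significance less than half the time; and the trial has 80% power for a 0.65 SD difference. The gap is the absence of a criterion.

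**Conclusion.** The concern holds in a limited form. The within-arm *t*-tests for CAPS-5, ITQ and DES are not derived from the stated model and, on their natural reading, sit badly with the intention-to-treat basis. The likely bias is modest: 0.05 to 0.10 SD at 10% loss and 0.09 to 0.18 SD at 18%, resting on assumed changes in completers and dropouts. More important, these tests and the PCL-5 time effect measure change and cannot attribute it to treatment, as the article partly admits. The comparable-effect-sizes argument has no criterion. With half-widths of 0.39 SD (95%) and 0.48 SD (98.3%), which rest on 39 analysed per arm and 25% of variance explained, a null difference leaves room for a deficit of nearly half an SD.

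The sample size and the planned between-arm comparison are unaffected. Nothing here shows that the trial was meant as a non-inferiority study.

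**What to change.** 1. Replace the *t*-tests in section 2.6.1.1 with T0–T8 and T0–T12 contrasts per arm from one longitudinal model. T0, T8 and T12 are all outcomes, baseline means are constrained equal across arms (justified because randomisation follows the baseline assessment), and all randomised participants are included. The same model supplies the between-arm contrasts at T8 and T12. It relies on data being missing at random, which should be stated.
2. Report these contrasts, and the PCL-5 time effect, as within-arm change and not as evidence of efficacy.
3. Report between-arm differences with confidence intervals and do not infer comparability from non-significance. Before data are examined, either state and justify a margin smaller than the 0.65 SD that the plan itself calls clinically meaningful, or drop the inference. A margin as wide as 0.65 SD would let a deficit just short of that difference pass as comparable. At margins below about 0.55 SD the trial has less than 80% power, so an inconclusive result must be an accepted outcome.

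The cost is model specification and reporting wording, with no extra participants or visits. Some statements of effectiveness become change from baseline, and some statements of comparability become inconclusive.

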##### 2.6.1.2. Outcome measures PCL-5, BDI-II, BSI, and AAQ-II

For the outcome measures administered (bi)-weekly, a multilevel model will be performed. The baseline values will be included as covariate in the model. It will be investigated if the treatment conditions are effective in reducing self-reported PTSD symptoms (PCL-5), comorbid symptoms (BDI-II and BSI) and experiential avoidance (AAQ-II) over time. To investigate the differential effectiveness of the treatments, a Time × Condition interaction will be tested with the outcome measures as dependent variables. To investigate the effectiveness of the treatments, the effect of time will be tested with the outcome measures as dependent variables.

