#### 2.3.3. Assessments

At baseline assessment (T0), the CAPS-5 will be administered by a trained therapist, along with the Life Events Checklist for DSM-5 (LEC-5). The International Trauma Questionnaire (ITQ), PTSD Checklist for DSM-5 (PCL-5), Dissociative Experiences Scale (DES), Beck Depression Inventory-II (BDI-II), Brief Symptom Inventory (BSI), and the Acceptance and Action Questionnaire-II (AAQ-II) will be administered digitally. The baseline assessment takes approximately 90 min. After the baseline assessment and the session where the treatment plan is drawn up, a 6-week treatment phase commences during which participants fill out questionnaires weekly prior to the treatment sessions (T1-6). Questionnaires include the PCL-5, BDI-II, BSI, and AAQ-II and take approximately 30 min in total to complete. After the first treatment session (T2), a questionnaire about treatment acceptability is administered. After the treatment phase, a 12-week phase commences where no actual treatment is delivered, but participants fill out the PCL-5, BDI-II, BSI, and AAQ-II bi-weekly (T7-12). The treatment acceptability questionnaire is administered again at T7. The CAPS-5, ITQ, and DES are administered 4 weeks after treatment is completed (T8), and 12 weeks after termination of treatment (T12). To minimize missing data, reminders will be sent out to the participants to fill out the questionnaires. For a complete overview of the timing of the interventions and assessments, see Figure 1.

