##### 2.6.1.3. Moderation analyses

To investigate whether treatment effect is moderated by baseline characteristics (baseline CAPS-5, PCL-5, DES, BDI-II, AAQ-II scores, and CPTSD diagnosis), Condition × Time × Moderator interaction effects will be tested with the primary outcome measures (CAPS-5, ITQ, and PCL-5) as dependent variables.

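### For PCL-5 and the other repeatedly measured questionnaires, baseline entered as a covariate main effect does not adjust the Time × Condition test; a Baseline × Time term would

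*Protocol article*

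**What the plan says.** Section 2.6.1.2 covers the four questionnaires completed weekly during treatment and every two weeks afterwards. Its provision for baseline is "The baseline values will be included as covariate in the model". Differential effectiveness is then examined as follows: "a Time × Condition interaction will be tested with the outcome measures as dependent variables". Section 2.6 describes the model: "In Level 2 of the model, the intercepts and slopes of the growth trajectories vary between participants".

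PCL-5 is among the primary measures. It is listed in 2.4.1, and 2.6.1.3 speaks of "the primary outcome measures (CAPS-5, ITQ, and PCL-5) as dependent variables".

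Two other places bear on the point:

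- Section 2.6.1.1 (CAPS-5, ITQ, DES) uses the same covariate sentence, but compares estimated average scores between arms at T8 and T12 rather than an interaction.
- Section 2.5 gives a reason for the covariate, for CAPS-5: "To increase the power, we will include the baseline CAPS-5 score as a covariate in the analyses".

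**The concern.** A covariate main effect adjusts a comparison of levels. It does not adjust a comparison of changes over time. The same covariate sentence therefore works in 2.6.1.1 and has no effect on the arm comparison in 2.6.1.2. A reader would take the PCL-5 comparison to be baseline-adjusted when the tested effect is not.

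Two things are at stake, and both depend on whether the starting score predicts change. The first is precision: variance in slopes that baseline could explain stays in the error. The second is sensitivity to the allocation actually drawn. If participants who start higher fall further, an arm that starts higher by chance shows a steeper fall, and the model as written does not correct for it.

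**Working it through.** **1. Reproducing the plan's own figure.** Inputs from section 2.5: "The power analysis is based on a two-sided *t*-test"; "Bonferroni-corrected alpha for the three pairwise comparisons = 0.0167 (0.05/3), power = 0.80 and Allocation ratio = 1"; d = 0.65; baseline expected to explain about a quarter of the post-treatment variance.

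- Adjusted effect: 0.65/√(1 − 0.25) = 0.751.
- Noncentral-t power at 39 per arm: 80.4%, so n = 39 and N = 3 × 39 = 117.
- With 10% dropout: 117/0.90 = 130.

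The stated figures reproduce. They concern the CAPS-5 post-treatment comparison.

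**2. Why the main effect cancels.** Let participant i have baseline value B(i), contributing βB(i) at every visit. Any contrast over time has weights w(t) that sum to zero, so the contribution is βB(i)·Σw(t) = 0. This holds for a linear slope and for categorical visits. In generalised least squares with complete data, the interaction estimate and its variance equal those from a model without baseline, whatever the within-person covariance.

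**3. Numerical check.** There were 60 simulated trials per scenario, each with 3 × 39 participants, visits T1 to T12, and fitted random intercepts and slopes as in section 2.6. The covariance, visit spacing and missingness are assumptions.

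| Baseline in model | Mean SE, complete data | Mean SE, with missing data* | Correlation of estimate with baseline imbalance, complete data | Same, with missing data* |
|---|---|---|---|---|
| None | 0.243 | 0.271 | −0.50 | −0.28 |
| Main effect | 0.243 | 0.272 | −0.50 | −0.26 |
| Main effect + Baseline × Time | 0.228 | 0.255 | −0.01 | 0.12 |

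*About 20% dropout plus 5% intermittent missingness.

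With complete data, the largest difference between the estimates in the first two rows was 3 × 10⁻¹⁴. With missing data the equality is only approximate, but the main effect still brings essentially no gain.

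**4. Size.** The article gives no PCL-5 slope effect and no correlation r between baseline and change. As an assumption, take a difference of 0.65 SD of the slope, n = 39 per arm and alpha = 0.05/3. Power with the added term uses d = 0.65/√(1 − r²); power as written uses d = 0.65 throughout.

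| r | d with Baseline × Time | Power with term | Power as written |
|---|---|---|---|
| 0 | 0.650 | 66% | 66% |
| 0.1 | 0.653 | 67% | 66% |
| 0.2 | 0.663 | 68% | 66% |
| 0.3 | 0.681 | 71% | 66% |
| 0.4 | 0.709 | 75% | 66% |
| 0.5 | 0.751 | 80% | 66% |

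**5. Sensitivity to imbalance.** The chance difference in mean baseline between two arms of 39 has SD √(2/39) = 0.23 baseline SD. An imbalance of that size moves the slope difference by r × 0.23 slope SD: 0.07 at r = 0.3 and 0.11 at r = 0.5. The standard error of the unadjusted slope difference is also 0.23 slope SD, so the shift is r standard errors.

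**The case against.** **The text does not say main effect only.** This is true: a fuller plan may cross baseline with time. But the article does fix both the covariate and the test, and where it wants a baseline score crossed with Time it writes that out, in the separate moderation analysis of 2.6.1.3. A main effect is the plain reading. The moderation model would include baseline PCL-5 with Time, but it does not replace the arm comparison in 2.6.1.2.

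**Section 2.5 promises nothing for this test.** This stands. A reader might infer that the article contradicts its own power statement or that the trial is undersized. It does not: the power gain is claimed for baseline CAPS-5 and a post-treatment comparison of means, and 2.6.1.1 delivers it.

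**The size may be small.** This also stands. A baseline-to-level correlation of 0.5 is not a baseline-to-change correlation of 0.5. Illustration, all values assumed: baseline-to-end and T1-to-end correlations of 0.5; baseline-to-T1 correlation ρ of 0.7 to 0.8, plausibly high because "participants fill out questionnaires weekly prior to the treatment sessions (T1-6"), so that T1 precedes the first session; end SD k = 1.0 to 1.4 times the T1 SD. Then r = (0.5k − ρ)/√(k² + 1 − k), which runs from 0 (k = 1.4, ρ = 0.7) to −0.30 (k = 1.0, ρ = 0.8). The gain is then 0 to about 5 points of power.

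**The test is not biased.** Correct. A reader might infer that chance imbalance makes the result wrong or inflates false positives. Under randomisation, type I error averaged over allocations is not inflated; what remains is sensitivity conditional on the imbalance observed.

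**Contrasts of level at T8 or T12 are already adjusted.** Largely so: a main effect enters any arm comparison of level taken from the model. The gap concerns the interaction.

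**Conclusion.** The point holds in a limited form. As 2.6.1.2 reads, the Time × Condition test for PCL-5, BDI-II, BSI and AAQ-II is not baseline-adjusted. The cancellation is exact for complete data, near-exact otherwise, and independent of how time is coded. The planned test is valid, but it may be less efficient than it could be and more sensitive to chance imbalance.

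The cost in power is between nothing (r = 0) and about 14 points (r = 0.5), and 0 to 5 points for r between 0 and 0.3. These figures borrow the CAPS-5 effect size of 0.65 for a PCL-5 slope, which the article does not do; the r = 0.5 row also borrows its quarter of variance. They show a range and are not an estimate for this trial. The 39/117/130 sample size and the comparisons in 2.6.1.1 stand as written.

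**What to change.** In 2.6.1.2, add the centred T0 value of the same outcome crossed with Time, coded as in the model, alongside the baseline main effect. Time × Condition is then adjusted for the starting score. Alternatively, define differential effectiveness for these four outcomes as baseline-adjusted arm differences at prespecified visits, as 2.6.1.1 already does. If a fuller plan already contains the term, one clarifying sentence is enough.

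The cost is a sentence of analysis text and one degree of freedom per model, or a few if time is categorical, with no new data. If baseline does not predict change, nothing is gained. The change should be settled before outcome data are analysed by arm.

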### 1.4. Current study

The available literature shows promising results regarding both EMDR 2.0 therapy and the Flash technique. However, for EMDR 2.0 and the Flash technique, a randomized controlled trial with participants diagnosed with PTSD is still lacking. Therefore, the goal of the present study will be to investigate EMDR 2.0 and the Flash technique in a sample of participants diagnosed with PTSD, and to determine their relative effectiveness, when compared with each other and standard EMDR therapy (38) as an active control condition. We chose EMDR therapy as a comparator, because it is one of the first-choice interventions for PTSD according to the international treatment guidelines (50). This allows for direct comparison between the experimental conditions and the extensively studied EMDR therapy. The proposed study has three aims. Firstly, we will determine the differential effectiveness of EMDR therapy, EMDR 2.0, and the Flash technique. More specifically, we will investigate which of these treatment conditions is most effective in reducing (complex) PTSD symptoms and comorbid psychiatric symptoms, as well as the loss of the diagnostic status of PTSD. In addition, we will investigate whether EMDR 2.0 and the Flash technique are effective treatments, by inspecting changes in these outcomes over time. We will also determine the moderators of effectiveness. The moderators that will be investigated are PTSD symptom severity, symptoms of depression and dissociation, experiential avoidance, and the presence of a complex PTSD diagnosis. To this end, identifying potential moderators can help to indicate which treatment option is most suitable for different types of patient characteristics. Secondly, we will investigate the differential efficiency of the three treatments. Thirdly, we will investigate whether the treatments differ in terms of treatment acceptability.

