There is not enough evidence to have *a priori* expectations with regards to the differential effectiveness of standard EMDR therapy compared to EMDR 2.0 or the Flash technique. Based on the results of earlier research on EMDR 2.0 and the Flash technique [e.g., (39, 48)], we expect that all interventions will be effective in terms of a significant reduction of (complex) PTSD symptoms and loss of diagnostic status. We also expect that all interventions will be effective in reducing the symptoms associated with PTSD. Considering the moderators, we expect that participants who show higher baseline symptoms of depression, will experience more difficulties in retrieving positive memories based on studies suggesting a negative memory bias in individuals with depression (51, 52). Therefore, we expect them to benefit less from the Flash technique than from EMDR therapy or EMDR 2.0. Furthermore, we expect participants who show relatively higher levels of experiential avoidance (defined as attempts to avoid thoughts, feelings, memories, physical sensations, and other internal experiences) and symptoms of dissociation at baseline, will benefit more from the Flash technique than from EMDR therapy. The reasoning underlying this hypothesis is that during the Flash technique only brief exposure to traumatic material is needed (42). Therefore, participants who are more avoidant, or tend to dissociate, will likely have less difficulty performing the Flash technique, than EMDR therapy. Based on the results of Matthijssen et al. (39), EMDR 2.0 is expected to be more efficient than standard EMDR therapy in treating traumatic memories and PTSD symptoms. Based on the preliminary findings of Brouwers et al. (48), we expect that the Flash technique will be rated as more acceptable by patients than standard EMDR therapy.

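### In 2.6.1.2 the effectiveness of each treatment is tested by a single time effect from a three-arm model, which does not test change within each arm

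*Protocol article*

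**What the plan says.** Section 2.6 of the protocol article sets up one model for all arms: "A multilevel model will be performed with Treatment Condition (EMDR therapy vs. EMDR 2.0 vs. Flash technique) and Time" are its predictors. Section 2.6.1.2 applies it to the four scales given weekly or bi-weekly and assigns one test to each of two questions.

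- Do the treatments differ? "To investigate the differential effectiveness of the treatments, a Time × Condition interaction will be tested with the outcome measures as dependent variables".
- Do the treatments work? "To investigate the effectiveness of the treatments, the effect of time will be tested with the outcome measures as dependent variables".

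The second question is about individual arms. Section 1.4 says "we will investigate whether EMDR 2.0 and the Flash technique are effective treatments, by inspecting changes in these outcomes over time", and states the hypothesis that "we expect that all interventions will be effective in terms of a significant reduction of (complex) PTSD symptoms and loss of diagnostic status". Section 2.6.1.2 itself asks about the treatment conditions in the plural. It names no within-arm contrast or simple slope, and no rule for reading the time effect when the interaction is significant.

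For the CAPS-5, ITQ and DES the text is different. In section 2.6.1.1 "the average scores will be estimated for the outcome variables at each time point for the three conditions", so estimates by arm are part of that analysis.

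**The concern.** In a model with Condition, Time and their interaction, the time term has one of two meanings. With averaged coding, or with the interaction left out, it is the mean change over the three arms. With dummy coding and the interaction in the model, it is the change in whichever arm is the reference. Neither null hypothesis is that EMDR 2.0 shows no change and, separately, that Flash shows no change. If EMDR, the active control, is the reference, the term tests neither new treatment.

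The PCL-5 is listed among the primary outcome measures, and the other three scales are secondary. The Discussion says that support for the effectiveness of EMDR 2.0 and Flash would give therapists additional options. On these four scales that support could come wholly from improvement in the other arms, including the established comparator.

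**Working it through.** **Sample size, reproduced first.** Section 2.5 gives d = 0.65, two-sided alpha 0.05/3, power 0.80 and about a quarter of the variance explained by baseline. The adjusted effect is 0.65/√0.75 = 0.751, and the non-centrality with 39 per arm is 0.751 × √(39/2) = 3.31. Power is 0.804 with 39 per arm and 0.792 with 38, so 39 per arm is confirmed. Then 3 × 39 = 117 and 117/0.90 = 130. The sample size is sound, and this point does not depend on it.

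**Set-up for the time test.** Each participant has one change score in units of its SD, a proxy for the individual slope. There are n = 39 per arm, N = 117, 114 residual degrees of freedom, and tests are two-sided at 0.05 (critical t = 1.98). Flash does not change; EMDR and EMDR 2.0 both improve by d. The document gives no expected change or SD of change for these scales, so the values of d are assumptions and a range is shown.

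**Formulas.**

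- Pooled time term: mean change (d + d + 0)/3 = 2d/3, standard error 1/√117, non-centrality (2d/3)√117 = 7.21d.
- Time term with EMDR as reference: non-centrality d√39 = 6.24d.
- Time × Condition (F, 2 and 114 df): non-centrality 39 × [2(d/3)² + (2d/3)²] = 39 × (2/3)d² = 26d².
- Flash's own contrast: non-centrality 0, so it rejects at the nominal 5%.

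**With the numbers in.** For d = 0.5 the three non-centralities are 3.61, 3.12 and 6.5, giving rejection rates of 95%, 87% and 61%. The full range is below. The percentages are from 20,000 simulated trials; the formulas agree to within about one percentage point. The fourth row is the share of trials in which the pooled term is significant and the interaction is not.

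| Assumed d in EMDR and EMDR 2.0 | 0.3 | 0.4 | 0.5 | 0.65 | 0.8 | 1.0 |
|---|---|---|---|---|---|---|
| Pooled time term significant | 58% | 82% | 95% | 99.7% | about 100% | 100% |
| EMDR-reference time term significant | 47% | 70% | 87% | 98% | 99.9% | 100% |
| Time × Condition significant | 25% | 41% | 61% | 84% | 96% | 99.7% |
| Pooled significant, no interaction warning | 43% | 48% | 37% | 16% | 4% | 0.3% |
| Flash's own contrast significant | 5% | 5% | 5% | 5% | 5% | 5% |

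This is a simplification. It uses one change score per person, not the repeated-measures model with a baseline covariate. The mismatch between test and question is a matter of what the term means and does not rest on the simulation.

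**The case against.** The strongest reply is that the sentence is loose, not wrong. It says nothing about coding or a reference arm, speaks of treatments in the plural, and could be read as the effect of time in each condition. How slopes are extracted from such a model is often left to the analysis plan, and this is a condensed article. That has some force: arm-wise effects may well be intended. But the text does name a test. It gives the interaction to one question and the time effect to the other, and the time effect of that model is not arm-specific. The wording needs correcting even if the intention was sound.

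A second reply is that the interaction, tested in the same model, would expose an unchanged arm. This holds in part. Section 1.1 describes large effects of EMDR on PTSD symptoms; at d = 0.8 the interaction is significant in 96% of trials and the silent error falls to 4%. At more modest improvements the protection is weak, the document does not link the interaction to the effectiveness conclusion, and a significant interaction says that arms differ, not which arm changed.

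Three stronger readings are tempting and not supported:

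- A reader might infer that an unchanged arm *would* be declared effective. No rule says that a significant time term makes every arm effective. If the unchanged arm is itself the dummy reference, the time term is that arm's own change and the error does not arise for it.
- A reader might infer that R and SPSS will test different hypotheses by default. Section 2.6 only lists both programs. It does not say that both fit this term or that defaults are used.
- A reader might infer that the whole effectiveness claim fails. Section 2.6.1.1 has estimates by condition for the CAPS-5, ITQ and DES.

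**Conclusion.** The point holds as a mismatch between a named test and its question, confined to the PCL-5, BDI-II, BSI and AAQ-II. The time effect in a three-arm model cannot show that EMDR 2.0 and Flash each changed, so an unchanged arm can be called effective on the strength of the others. The risk of this happening without a signal from the interaction is substantial when the other arms improve by 0.3 to 0.5 SD of change and small from about 0.8 SD. Those sizes depend on assumed improvements, 39 per arm and a change-score simplification; the mismatch itself does not. The wording should be changed before analysis, but the defect does not undermine the design.

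**What to change.** In section 2.6.1.2, replace the sentence that tests effectiveness by the time effect with: *Change over time will be estimated with a 95% CI and tested within each condition by arm-specific contrasts from the Time × Condition model, with a stated multiplicity adjustment across the three conditions (for example 0.05/3). A condition is said to show improvement on an outcome only on its own contrast, and this is interpreted as uncontrolled within-arm change.*

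The last clause follows the limitation in section 3, which acknowledges that there is no inactive control condition and that the design is therefore not ideal for showing effectiveness. A contrast within one arm does not remove that limit.

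No new data or model are needed. The cost is power. If all three arms improve by d, the pooled test has non-centrality d√117 and each arm's contrast d√39. At d = 0.3, 0.5 and 0.8 the pooled test at 0.05 has power of about 90%, over 99.9% and about 100%. Each arm's contrast has about 46%, 87% and 99.9% at 0.05, and about 29%, 75% and 99% at 0.05/3 (critical t = 2.43). That is the price of answering the question the article asks.
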